### 4.4. Randomization

Given the elevated risk of CMD, the reported benefit of intervention studies on mitigating CMD risk [36], including a preliminary report on the TLI [26], and the ethical imperative to provide effective interventions [37], all participants with SCI will undergo a TLI program modeled after the CDC-supported widely adopted National DPP. The intervention program will incorporate population-targeted exercise, nutrition, and behavioral support in the form of a detailed curriculum, all aspects of which have been tested in a federal grant program at the lead center. Following the completion of baseline assessments, caregivers will be randomized to one of two groups using a stratified approach to achieve equal numbers in persons caring for enrolled partners with paraplegia and tetraplegia. Randomization will be performed independently within each stratum by an independent senior researcher using a list generated by the ‘RAND’ function in Microsoft Excel (Microsoft, Miami, FL, USA). Blinding is not achievable in this intervention study, and therefore neither participants nor research staff will be blinded. Participants are randomly sorted based on generated random numbers—a binary response variable, 0 for the control curriculum group and 1 for the CCC group— and their allocation to groups depends solely on their position in the sorted order. This randomization procedure ensures that participants are allocated to the CCC and control groups in an unbiased and unpredictable manner. Randomization of caregivers serves scientific and ethical purposes by allowing for rigorous assessment and ensuring equitable access to the intervention. Caregivers (linked with their partners) randomized to the test condition will undergo a CCC containing information that is similar to that presented to, but independently taught from, their partners. Caregivers randomized to the control condition will learn a time-matched (i.e., attention/time-controlled) curriculum containing generic information on the overall benefits of exercise and nutrition but lacking any specific exercise/nutritional guidelines, self-management strategies, or nutritional/meal composition. This information will be tailored to people without disabilities and include information the caregiver might otherwise find on the internet. All caregivers, irrespective of randomization, will receive SCI-specific material so that they can provide the appropriate support and best care possible in the framework of the TLI.

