## 4. Materials and Methods

### 4.1. Trial Design

This is a prospective randomized, controlled, multi-center intervention adopting a within-subjects repeated measures design, examining persons with disability from SCI and their caregivers who will be co-enrolled as dyadic partners. Following eligibility screening, consent, and randomization (of caregivers only), participants will attend two preliminary sessions including wash-in and baseline assessments (serving as ‘own-control’) prior to beginning in one of the two intervention conditions. Two post-intervention assessments will be conducted, one immediately post-TLI (6 months) and one follow-up (12 months). The trial design is summarized below (Figure 1), was approved by the Human Subjects Research Office, Miller School of Medicine, University of Miami (Institutional Review Board No. 20151065, dated 20 July 2016), and is registered as a controlled trial (ClinicalTrials.gov, ID: NCT02853149 on 2 August 2016).

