### 4.3. Trial Recruitment

Candidates will be recruited by informal advertising, personnel referrals, and participant databases at both centers. The Miami Project maintains a database of individuals who have participated in past studies and volunteered additional participation. This is a searchable database under the management of the Director of Education. Institutional Review Board (IRB)-approved advertisements will be posted in the SCI/rehabilitation outpatient clinics at both centers. Basic information about the study status, such as active recruiting, closing, etc., will be searchable in the research section of each participating center’s website (http://www.themiamiproject.org/, (accessed on 2 August 2016); https://craighospital.org/programs/research/research-participation-opportunities, (accessed on 2 August 2016); and additional advertisements such as web blurbs and flyers will be distributed via emails and relevant social media accounts by each center. Upon initial contact, the study will be described and those interested in enrolling will be screened to ascertain eligibility. Written consent will be obtained during the initial on-site preliminary session, and participants will be informed that they can withdraw from the study at any time without consequence. Participants will be paid for their participation in this study. The total value of remuneration for participants at Miami will be USD 750, dispersed in four (4) payments: USD 150 after completion of screening and enrollment, USD 150 after 3 months post training, USD 150 after 6 months of training, and a balance of USD 300 after all data collection is completed at 12 months. The total value of remuneration for Craig participants will be USD 550, dispersed in four (4) payments: USD 100 after completion of screening and enrollment, USD 100 after 3 months post training, USD 100 after 6 months of training, and a balance of USD 250 after all data collection is completed at 12 months. This is primarily designed to reimburse travel expenses and thank them for any inconvenience caused. Compensation differences between sites reflect differences in the cost of living and compensation structures in place at each site to incentivize but not coerce participants.

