### 5.1. Description of Testing for SCI Participants

Anthropometry: Primary Outcome: Body Mass (BM): Participants will be weighed both in and out of their wheelchairs on a calibrated wheelchair scale, and the outcome of mass will be expressed as the average of the two measurements. Height/Waist Circumference/BMI: Height will be measured on a plinth to the nearest 0.25 inch. Waist circumference will be measured using a Gulick tension-regulated tape measure at the level of the umbilicus and recorded to the nearest 0.25 inch. Height [m] and weight [kg] will be used to calculate the body mass index (BMI) in kg/m^2^.Cardiorespiratory Endurance: Cardiorespiratory endurance will be assessed as the peak oxygen consumption (VO_2_peak) on an arm crank ergometer using the open circuit spirometry method. Participants will refrain from exercise for 24 h prior to testing. Ten minutes of quiet rest will follow the preparation and precede the exercise to acquire the baseline values. A peak continuous graded exercise test will determine the VO_2_sub-peak/peak, HRsub-peak/peak, and ratings of perceived exertion (RPE; categorical ratio (0–10) scale) at subpeak and peak work. The participants will perform work using a calibrated electronically braked arm crank ergometer (Angio, Lode BV, Groningen, The Netherlands), or the equivalent heart rate and oxygen consumption will be recorded continuously from baseline through recovery. HR will be measured with standard electrocardiography, while expired respiratory gases will be collected and analyzed with an online open-circuit metabolic cart (Vmax ENCORE, CareFusion, San Diego, CA, USA) or equivalent. The participants will position their wheelchair at a distance from the arm crank ergometer where their arms can remain slightly flexed at the furthest point from the trunk, and wedges will be placed under the rear wheels to restrict chair movement. Individuals with tetraplegia will have their hands affixed to the arm cranks with hand wraps and athletic tape. Thereafter, the participants will begin cranking on the arm crank ergometer at an initial load of 5 W and will be instructed to maintain a cadence of 55–65 rpm. A digital display will provide real-time revolutions per minute (rpm) feedback.

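### Section 4.4 allocates caregivers by sorting participants, which does not fit rolling entry or secure equal arms; with injury level as the only stratum, the CCC–control contrast is open to chance imbalance by site

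*Protocol article*

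**What the plan says.** **Stratum.** Section 4.4 names one stratification factor, the injury level of the SCI partner: "using a stratified approach to achieve equal numbers in persons caring for enrolled partners with paraplegia and tetraplegia". Sections 4.1 and 4.2 describe a multi-center trial at two sites. Site is not mentioned in the randomisation text.

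**Mechanism.** "Randomization will be performed independently within each stratum by an independent senior researcher using a list generated by the" Excel RAND function. Then: "Participants are randomly sorted based on generated random numbers", and "their allocation to groups depends solely on their position in the sorted order". The same sentence describes the random numbers as a binary variable, with 0 for the control curriculum and 1 for the CCC. No cut-point of the sorted order and no block is given.

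**Timing.** Section 4.4: "Following the completion of baseline assessments, caregivers will be randomized to one of two groups". Section 4.1 has the opposite order: "Following eligibility screening, consent, and randomization (of caregivers only), participants will attend two preliminary sessions including wash-in and baseline assessments".

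**Site differences in the text.** Section 4.3 pays USD 750 at the lead site and USD 550 at the second: "Compensation differences between sites reflect differences in the cost of living and compensation structures in place at each site". Section 5.1 allows substitute equipment, for example "Vmax ENCORE, CareFusion, San Diego, CA, USA) or equivalent".

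**The concern.** Every SCI participant receives the TLI, so the caregiver allocation creates the only randomised comparison in the trial. Objective III and the caregiver contrast under Objective II depend on it, with 30 dyads enrolled and about 24 expected to be analysed.

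Two things look wrong. First, the parts of the stated procedure do not fit together. Sorting people and assigning by rank requires all of them to be known at once, whereas a binary draw defines no rank and does not hold the arms equal. Second, with so few dyads and two centres, nothing in the allocation keeps the arms balanced by site. Any site effect on outcome then adds avoidable noise to a contrast that is already imprecise.

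**Working it through.** **Inputs.** From the article: 30 dyads, 20% attrition and an analytic sample of 48 people (Section 4.5); two sites (Section 4.2); one stratum factor (Section 4.4). Assumed, because not stated: 1:1 arms of 15; 15, 10 or 6 dyads at the second site; strata of 15 where a stratum size is needed; a site effect of 0.5 SD for illustration.

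**The plan's own figures.** The article gives none for allocation or site balance. The attrition step reproduces: 60 × 0.8 = 48 people, that is 24 dyads, or 12 per arm.

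**Step 1. Which readings of Section 4.4 secure equal numbers?**

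- *Sort a complete stratum and halve it.* Arms are equal to within one, but the whole stratum must have finished baseline before anyone is assigned. Section 4.3 screens candidates on first contact at two centres, Table 1 gives each participant visits at months −2 and 0, and Section 6.1 then starts a supervised 24-week programme. Holding early dyads until the last one is ready would make their month-0 data stale. Entry one dyad at a time is an inference from this, but a strong one.
- *Independent 0/1 draw per caregiver.* X ~ Binomial(30, 0.5):
  - P(15:15) = C(30,15)/2^30 = 155,117,520/1,073,741,824 = 0.144.
  - P(18:12 or worse) = 2·P(X ≥ 18) = 0.362.
  - In a stratum of 15, P(10:5 or worse) = 2 × 4,944/32,768 = 0.302.
- *Balanced list made in advance, no blocks, only partly used.* For a list of 30 per stratum with 15 places used, X ~ Hypergeometric(30, 15, 15): the arms differ by 3 or more with probability 0.466 and by 5 or more with probability 0.143.

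Only the first reading delivers equal numbers reliably, and it is the one that does not fit rolling entry.

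**Step 2. Site balance when site is ignored.** With arms of 15:15 and m dyads at the second site, the number of those in the CCC arm is X ~ Hypergeometric(30, 15, m). The difference in site share between arms is |2X − m|/15.

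| m | P(difference ≥ 20 points) | P(difference ≥ 33 points) |
|---|---|---|
| 15 | 0.466 | 0.143 |
| 10 | 0.245 | 0.050 |
| 6 | 0.169 | 0.017 |

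Exact balance within injury strata does not help. With two strata of 15 and a near-even site split in each, the corresponding figures for m = 15 are 0.474 and 0.149.

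**Step 3. What this does to the contrast.** Shift = site effect × difference in site share: 0.5 × 0.20 = 0.10 SD, or 0.5 × 0.333 = 0.17 SD. The standard error at 12 per arm is √(1/12 + 1/12) = 0.41 SD. If site is adjusted for instead, the variance of the contrast rises by 1/(1 − r²), where r is the correlation of arm with site. For m = 15, r equals the difference in share, so the factor is 1/(1 − 0.04) = 1.04 at 20 points and 1/(1 − 0.111) = 1.13 at 33 points.

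**Step 4. After the change.** In a simulation of 20,000 runs, half the dyads had tetraplegia and about 50%, 33% or 20% were at the second site, with the count varying between runs:

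- Blocks of 4 by injury level only: P(difference ≥ 20 points) = 33%, 30%, 21%.
- Blocks of 4 by site × injury level: 0.2%, 0.2%, 0.5%.
- Overall arm sizes differing by 4 or more under site × injury level: about 8–9% with blocks of 4, about 1.5% with blocks of 2.

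**The case against.** The best defence has four parts.

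1. *Chance imbalance is not bias.* A reader might infer that the CCC effect is confounded with site. The article does not support that: leaving site out of the strata produces only random imbalance, which is already part of the randomisation error and can be adjusted for in an analysis plan that is not shown. This stands. On the assumed 0.5 SD site effect, the shift is a quarter to two fifths of a standard error (0.10/0.41 and 0.17/0.41). Low power is the larger limitation of this contrast: about 20% for a standardised difference of 0.48 with 12 per arm.

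2. *The site differences are thin.* Payment differs by site but not by arm. Permission to use equivalent equipment does not say that the sites use different machines, and separate coaches at each site are plausible but not stated. Biochemistry is done centrally, and a stable equipment offset largely cancels in within-person change. This also stands; the documents give no estimate of a site effect.

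3. *The article does not promise equality outright.* A reader might take Section 4.4 to claim that its procedure guarantees equal arms. Its assurance concerns unbiased and unpredictable allocation; equal numbers are the aim of the stratification. The point here is only that the described steps do not secure that aim.

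4. *A charitable reading exists.* The 0 and 1 could be arm codes on a list made in advance and ordered by RAND, with block details left to the full protocol. That would explain part of the text, but not the statement that the participants themselves are sorted and assigned by rank. The article commits itself to a procedure, and as written that procedure does not work for sequential entry.

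**Conclusion.** The point holds in a limited form. The mechanism in Section 4.4 is internally inconsistent. Its only reading that reliably yields equal arms needs a complete roster, while a plain 0/1 draw gives 15:15 in 14% of cases. With injury level as the only stratum, there is a 17% to 47% chance that the arms differ by 20 points or more in site share, across second-site counts of 6 to 15.

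The consequence is weaker balance and precision in the CCC–control contrast for Objectives II and III. The pre–post body-mass comparison in SCI participants, all of whom receive the TLI, does not depend on this allocation. The conclusion rests on rolling entry, which is inferred, and on an assumed site split. The probabilities move with the split; the inconsistency in the mechanism and in its timing does not. It merits an amendment but does not invalidate the trial.

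**What to change.** - Replace the sorting description in Section 4.4 with a list generated once, before first enrolment, in permuted blocks of randomly varying small size (2 and 4) within the four site × injury-level strata. The independent researcher already named holds it and releases one assignment per dyad.
- Include site and injury level in the CCC–control comparison, as the randomisation strata.
- Reconcile Section 4.1 (randomisation before wash-in and baseline) with Section 4.4 (after baseline). In an unblinded trial, release after a dyad's month-0 assessment keeps the baseline measures free of knowledge of the arm.

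The cost is a short amendment and one new list, with no new staff or data. There are two small downsides. Small blocks are partly guessable in an open trial, which varying sizes and release by someone outside the study team limit. Incomplete blocks in four small strata can also leave the arms slightly unequal overall. Blocks of 2 and of 4 were simulated separately (a difference of 4 or more in about 1.5% and 8–9% of runs); a mixture was not simulated but should fall between these.

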## 3. Hypothesis

I.Participants with SCI will have (a) lower body mass, (b) reduced cardiometabolic risks and inflammatory stress, (c) improved cardiorespiratory fitness and strength, (d) improved multidimensional function, pain, quality of life, and self-efficacy, (e) overall program adherence, and (f) greater life satisfaction following TLI;II.Caregivers of persons with SCI will have (a) lower body mass, (b) reduced cardiometabolic risks and inflammatory stress, (c) improved cardiorespiratory fitness and strength, (d) improved multidimensional function, pain, quality of life, and independence, and (e) reduced perceived caregiver burden, following TLI;III.Participants with SCI will have better outcomes on all of their tested hypotheses if their caregiver partner receives the CCC and not the control curriculum.

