### 4.2. Trial Setting

All human testing will take place at the lead center in the Lois Pope Life Center at the Miami Project to Cure Paralysis at the University of Miami’s Miller School of Medicine, and at a secondary specialty SCI rehabilitation facility at Craig Hospital (Denver, CO, USA). All biochemical analyses will take place at the Diabetes Research Institute, Division of Endocrinology, Diabetes and Metabolism at the University of Miami Miller School of Medicine.

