In one-minute work stages [42], the resistance will increase at a rate of 5 W for all women and individuals with tetraplegia, or 10 W for individuals with paraplegia. The participants will continue until volitional fatigue, manifesting as either a verbal or nonverbal communication of the desire to stop or an inability to maintain cadence above 55 rpm. Upon cessation, participants will rest quietly for 10 min. The exercise termination will be based on the American College of Sports Medicine Guidelines for Exercise Testing and Training [ACSM, 9th Edition], with peak work defined as volitional exhaustion, the inability to maintain the targeted workload, or when increasing the workload fails to further increase VO_2_. The expired gases will be continuously analyzed using an open circuit indirect calorimetry system (Encore^®^, with Cardiosoft^®^ EKG monitoring, VIASYS, Inc., (Conshohocken, PA, USA) or equivalent). EKG rhythm will be continuously monitored to screen ischemia, rhythm disturbances, and signs/symptoms of exertional intolerance.

Perceived exertion (Borg Categorical-Ratio (0–10) Scale) will be obtained at the end of each exercise stage and at test termination.

3.Strength: Strength will be measured as upper-extremity dynamic strength on a Helms Equalizer 7000 multi-station exerciser (Helms Distributing, Polson, MT, or equivalent resistance equipment) using the same maneuvers adopted for training (Table 2). Subjects will be instructed to perform eight repetitions of each maneuver with each repetition lasting six seconds (3 s concentric, 3 s eccentric). If eight repetitions are completed in a controlled fashion, the weight will be increased and the exercise repeated. Incremental increases in weight (5 kg each for paraplegia, 2.5 kg for tetraplegia) will be added until eight controlled repetitions cannot be completed. The 1-RM will be calculated by the Mayhew regression equation [43], as we have previously reported [26]: 1-RM = Wt/(0.533 + 0.419e(− 0.055 × Reps))

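### The protocol rules out blinding for all research staff, but laboratory staff, diet-record coders and the analyst could be masked to caregiver allocation, and testers of SCI participants could be where staffing allows

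*Protocol article*

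**What the plan says.** All references are to the protocol article.

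- **Blinding (4.4):** the article holds that blinding cannot be achieved and concludes that "neither participants nor research staff will be blinded". No role is excepted, and no other section describes a masked assessor, laboratory or analyst.
- **What is randomised (4.4):** "caregivers will be randomized to one of two groups using a stratified approach", namely CCC or a time-matched control curriculum. Caregivers are taught separately from their partners.
- **Treatment of SCI participants (4.4):** "all participants with SCI will undergo a TLI program modeled after the CDC-supported widely adopted National DPP".
- **What the randomisation serves (3):** Hypothesis III expects SCI participants to have "better outcomes on all of their tested hypotheses if their caregiver partner receives the CCC and not the control curriculum". Objective II uses the same two arms for caregiver outcomes.
- **Laboratory and data handling:** "All biochemical analyses will take place at the Diabetes Research Institute" (4.2). Diet records are analysed at the lead centre (5.1). De-identified data carry a study ID (8.3).
- **Testing of SCI participants (5.1):** for the arm-crank test, "The participants will continue until volitional fatigue, manifesting as either a verbal or nonverbal communication of the desire to stop". Strength testing ends when eight controlled repetitions can no longer be done.

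**The concern.** The sentence in Section 4.4 moves from a true premise to a conclusion that is too wide. Participants know what they are taught and coaches know what they teach, so neither can be blinded. A laboratory technician, a diet coder, an analyst or a person running an arm-crank test on an SCI participant is in a different position.

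At stake is the only randomised contrast in the trial. Staff who know the caregiver's arm can, without intending to, vary encouragement, the decision to end a test, the judgement that a repetition was controlled, the reading of a blot, or choices made during analysis. Randomisation does not remove differences that arise after allocation in this way.

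**Working it through.** The plan gives no figure on this point, so the check is mainly one of reading. A short illustration of scale follows.

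**Step 1. Who has to know the caregiver's arm?**

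| Role | Needs the arm? | Basis in the protocol |
|---|---|---|
| Participants, coaches | Yes | They receive or deliver the curriculum (4.4, 6.1, 6.2) |
| Laboratory | No | Assays are central (4.2) |
| Diet-record coders | No | Coding is at the lead centre (5.1) |
| Analyst | Not before database lock | Data are held under study IDs (8.3) |
| Testers of SCI participants | No | All SCI participants have the same treatment; partners are taught separately (4.4) |
| Testers of CCC caregivers | Hard to avoid | The same personnel oversee caregiver training and testing (6.2) |

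The diet records are also meant to show dietary drift in the caregiver control arm (5.1). That tabulation by arm can be made after coding, so it does not require the coder to know the arm.

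**Step 2. Which SCI outcomes could masking help?** Table 1 has 16 rows for SCI participants:

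- Body mass: 1 row, read from a calibrated scale.
- Blood measures: 3 rows. Lipids and A1C use automated methods. The inflammatory markers include Western blotting, which leaves room for judgement.
- Endurance and strength: 2 rows, dependent on effort and on the tester.
- Wholly or mainly participant-reported: 10 rows (food log, SCI-FI, CHART, pain data set, NPSI, MPI-SCI, SCIM, exercise self-efficacy, CEQ, LSQ-9).

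Check: 1 + 3 + 2 + 10 = 16. Tester masking therefore helps mainly in the two fitness rows and in waist circumference, which is measured by hand but has no row of its own. Masked coding helps the food log at the coding stage, and masked reading helps the inflammatory row. Masked analysis limits arm-driven choices across all rows.

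**Step 3. Which analyses are exposed?** Section 4.5 bases the sample size on the pre-to-post change in body mass in the SCI group. Caregiver arm does not enter that contrast, so masking to arm leaves it unchanged. The exposed analyses are the CCC-versus-control comparisons.

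**Step 4. Illustration of scale (the shift is assumed).** Inputs from 4.5 are 30 dyads and 20% attrition. 30 × 0.8 = 24 dyads, or 12 per arm if the arms are equal.

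- Standard error of a standardised mean difference: sqrt(2/12) = 0.41.
- An assumed tester shift of 0.2 SD is 0.2/0.41 = 0.49 standard errors; 0.3 SD is 0.73.
- Two-sided 5% t test, 22 degrees of freedom, noncentrality b × sqrt(12/2), no true effect:

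| Assumed shift b (SD) | Actual type I error |
|---|---|
| 0 | 5.0% |
| 0.1 | 5.6% |
| 0.2 | 7.6% |
| 0.3 | 10.8% |

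Nothing in the document says which row applies, or whether any shift would occur.

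**The case against.** The case against has several parts.

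- **The primary outcome is safe.** Body mass comes from a calibrated scale, and the powered contrast is pre versus post. This stands, and it limits the point to comparisons that the sample size was not built for.
- **Most SCI outcomes are self-reports.** A reader might infer from Table 1 that nearly every outcome is open to correctable tester bias. The table does not support that: about 10 of the 16 rows come from unblinded participants, and masking testers does little for them.
- **The fitness tests are constrained.** VO2 is measured by a metabolic cart, and stopping can also follow from cadence below 55 rpm or from VO2 failing to rise. Strength testing uses timed repetitions, fixed load steps and a regression equation. This narrows the room for influence. It does not close it, because a participant may stop by choice before those limits and encouragement can affect when.
- **Masking SCI testers may need staff the trial lacks.** A reader might infer that it can be done with no extra staff. The article gives no staffing plan for SCI testing, so this is not established. Participants may also disclose the arm. Hence the qualification: where staffing allows.
- **The small sample makes it worse.** This is tempting but wrong. A fixed bias is not averaged out at any size, and it is a smaller share of the standard error in a small trial: 0.2 SD is 0.49 standard errors at 12 per arm but 0.2/sqrt(2/100) = 1.41 at 100 per arm.
- **Objective II gains less.** Caregiver fitness testing would stay open. Masked laboratory work, diet coding and analysis would still help caregiver outcomes.
- **An article may leave masking details to a fuller document.** That would excuse silence. Here the article states a rule covering research staff without exception, and the rule does not follow from its stated reason.

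**Conclusion.** The point holds in a limited form. The blanket statement in Section 4.4 is justified for participants and intervention coaches. It is not justified for laboratory staff, diet-record coders or the analyst, who could be masked by controlling access to the allocation. Testers of SCI participants could also be left uninformed where staffing allows.

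The benefit is less detection and analysis bias in the CCC-versus-control comparison, mainly for Objective III. The powered pre-post body-mass contrast is unaffected, and bias in self-reports remains. The size of the avoidable bias cannot be derived from the document. The error rates of 5.6% to 10.8% rest on assumed shifts of 0.1 to 0.3 SD, equal arms and 12 per arm, and show scale only. This is a cheap improvement to the randomised comparison; it does not call the primary analysis into question.

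**What to change.** Replace the blinding sentence in Section 4.4 with:

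> Participants and intervention coaches are not blinded. Laboratory staff, diet-record coders and the analyst work from study IDs without allocation until database lock. Staff testing SCI participants are not told the caregiver's arm where staffing allows, and any coach-tester overlap or unmasking is recorded.

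To make this work, restrict the allocation list to the independent senior researcher who performs the randomisation and the caregiver coaches.

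The cost is protocol wording, an access rule and some care in scheduling. Sample size, alpha and power do not change. Masking of SCI testers will sometimes be broken by participants; recording when this happens lets readers judge how far it held.
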